**Secondary objectives**
To evaluate the association of gadget addiction with Deha and Manas Prakriti (physical and mental constitution) of the participant with the help of Ayusoft software. Manufactured by C-DAC (Centre for Development of Advanced Computing) To assess the impact of gadget addiction on social relationships and behaviors in the *DSM-5* scale.

#### Hypothesis

##### Null Hypothesis (H0)

Any intervention among the Medhya Rasayana and Ayurveda nonpharmacological intervention are not as effective as the control group in reducing gadget addiction in children.

##### Alternative Hypothesis (H1)

At least 1 intervention among the Medhya Rasayana and Ayurveda nonpharmacological intervention are more effective than the control group in reducing gadget addiction in children.

The purpose of this hypothesis is to determine whether the 3 interventions under comparison in the study differ in their efficacy. If statistically significant differences exist in the outcomes, researchers can ascertain them by testing the null hypothesis against the data gathered during the randomized controlled trial.

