**Primary objectives**
To evaluate the efficacy of Medhya Rasayana in gadget addiction with an internet addiction test scale, a digital addiction scale, and *DSM-5* (*Diagnostic and Statistical Manual of Mental Disorders* [Fifth Edition]).To evaluate the efficacy of Ayurveda nonpharmacological interventions in gadget addiction with an Internet addiction test scale, a digital addiction scale, and *DSM-5*.To assess the comparative efficacy of 3 therapeutic modalities in the management of gadget addiction by Internet addiction test scale and *DSM-5*.

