### Participants

The required sample size was calculated by using the following formula.

To evaluate the effectiveness of the therapeutic modalities for managing internet addiction, several key parameters are defined. The type I error rate () is set at 5% and the type II error rate (β) is set at 20%. The true proportion difference, represented by ε, is assumed to be 0. δ denotes the clinically relevant difference at 20% superiority. Initially, the proportion of individuals with internet addiction (P1) is 62.22% (0.622). After the intervention (P2), this proportion decreased to 36.2% (0.362). To determine the appropriate sample size for the study, a clinically accepted difference of 20% is used. The sample size is calculated according to the formula N=(1.64+0.84)2(0.622)(1–0.622) +0.362(1–0.362)/(0.20)2. Based on this formula, the required sample size is 72 individuals per group. To account for a 10% dropout rate, the sample size is increased to 80 per group.

Therefore, 80 participants will be recruited after randomization in each group from the Kaumarbhritya OPD of Mahatma Gandhi Ayurved College Hospital and specialty camps held in peripheral villages of Wardha city. A computer-generated random number table will be used to avoid selection bias in the study. The principal investigator will carry out the process of randomization and enroll the participants. To be eligible for participation, participants should fulfill the inclusion criteria as mentioned in Textbox 2. Patients having any characteristics of exclusion criteria will be excluded from participation in the study.

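### An at-least-one hypothesis over two arms and two comparative primary scales is set against a 5% error rate spent in full on a single comparison

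*Protocol article*

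**What the plan says.** Four parts of the Protocol article bear on this.

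- **Alternative Hypothesis (H1):** the claim to be supported reads "At least 1 intervention among the Medhya Rasayana and Ayurveda nonpharmacological intervention are more effective than the control group". The text that follows gives the purpose as finding out whether the three interventions differ in efficacy.
- **Primary objectives:** each Ayurveda intervention is to be evaluated with "an internet addiction test scale, a digital addiction scale, and" DSM-5. The third objective, which compares the three modalities, names only IAT and DSM-5. No scale is designated as leading.
- **Participants (sample size):** "The type I error rate () is set at 5" percent, with a type II error rate of 20%. The formula begins "N=(1.64+0.84)2(0.622" and leads to 72 per group, raised to 80 for 10% dropout.
- **Statistical Analysis:** repeated measures ANOVA and chi-square tests are named, and the choice of method remains open to advice from a statistician.

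Study Design and Table 1 add that group C is external: it consists of published cognitive behavioural therapy data and has no planned number of participants. Only groups P and N are randomised, 1:1.

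**The concern.** H1 is true if P beats control, if N beats control, or if both do. The comparative objective lets each of these be judged on two scales of equal standing, so up to four directional tests could support H1. The 5% in the sample size section is the rate for one such test. Nothing in the text links that figure to the hypothesis as a whole.

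Two things are at stake. If each test is run at 5%, a claim that some Ayurveda intervention outperforms control would be false more often than the stated rate suggests. If the tests are adjusted later, the 80% no longer describes each arm at the published sample size. H1, the primary objectives, the error rate and the sample size are all set out in the protocol itself, and as printed they do not fit together.

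**Working it through.** **Inputs.** All come from the Participants section: P1 = 0.622 ("the proportion of individuals with internet addiction (P1) is 62.22% (0.622"), P2 = 0.362 ("this proportion decreased to 36.2% (0.362"), a denominator difference of 0.20 ("a clinically accepted difference of 20% is used"), z values 1.64 and 0.84, and dropout of 10%. The correlations used below are assumptions, because the article gives none.

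**1. Reproduce the plan's figure.**
- Variance term: 0.622 × 0.378 + 0.362 × 0.638 = 0.2351 + 0.2310 = 0.4661.
- n = (1.64 + 0.84)² × 0.4661 / 0.20² = 6.1504 × 0.4661 / 0.04 = 71.66, rounded up to 72.
- With dropout: 72 / 0.90 = 80. Both figures reproduce.
- A two-sided 5% (z = 1.96) would give 91.5. So 72 rests on a one-sided 5% given wholly to one comparison.

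**2. False-claim rate, two arms, one scale, each at one-sided 5%.**
- Control taken as a fixed published value, tests independent: 1 − 0.95² = 9.75%.
- Tests sharing the control's sampling error, correlation 0.5 (as with a control of equal size): 1 − Φ₂(1.645, 1.645; 0.5) = 8.8%.

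**3. The same, two arms and two scales (four tests), from the multivariate normal.**

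| Assumed correlation between scales | Arms independent | Arms correlated 0.5 |
|---|---|---|
| 0.5 | 16.8% | 15.0% |
| 0.7 | 15.4% | 13.8% |
| 0.9 | 13.2% | 11.8% |

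**4. Power at 72 evaluable per group.** This keeps the plan's two-group formula and its 0.20 difference.
- Standard error = √(0.4661 / 72) = 0.0805, and 0.20 / 0.0805 = 2.486.
- One test at one-sided 5%: Φ(2.486 − 1.645) = 80.0%.
- Each arm at one-sided 2.5%: Φ(2.486 − 1.960) = 70.1%.
- At least one arm at 2.5% each, if both arms are effective: 1 − (1 − 0.7005)² = 91% if independent, 84% at correlation 0.5.
- To restore 80% per arm at 2.5%: 91.45, so 92 evaluable and 92 / 0.90 = 102.2, or 103 recruited per group.

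**The case against.** **The article gives a hypothesis, not a success rule.** A reader might infer that success will be declared on any one unadjusted test, so that the 5% is certainly exceeded. The documents do not support that. The text after H1 asks whether the three interventions differ, ANOVA is the named method, and one omnibus test on one scale would hold 5%. This stands, and the error rates above are therefore conditional. But an omnibus test has no direction and cannot by itself establish that an arm is better than control. With control taken from published data, the article also does not show how control would enter a participant-level ANOVA.

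**Adjustment is commonly left to the analysis plan.** This is true, and the absence of an adjustment rule is not the point here. A later split of the 5% would still change what 80% means at 72 per group.

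**The loss of power can be overstated.** A reader might say that 80% power fails once the error is controlled. For H1 as worded, the matching quantity is power for at least one arm, which is 84-91% if both work. The 70% applies to each arm separately, or to the case where only one works. It also depends on the 0.20 in the denominator. The plan's own proportions differ by 0.26, and at that difference power at 2.5% is Φ(0.26 / 0.0805 − 1.960) = 90%.

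**Two further readings go too far.** One counts three scales against control, but the digital addiction scale appears only in the single-arm objectives, so four tests are better supported than six. The other says that each arm was sized against control. P1 and P2 are described as proportions before and after intervention, and control has no planned number.

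**The external control is the larger problem.** This stands. No division of the 5% secures the error rate of a comparison with non-randomised published data.

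**Conclusion.** The point holds in conditional form. The plan's hypothesis can be met through two arms, its comparative primary objective has two scales without a leader, and its 5% covers one test. Testing each comparison at that level gives about 9-10% on one scale: 9.75% if the published control is treated as a fixed value, and less if its own error is shared by both tests. Over two scales it gives about 12-17%, for between-scale correlations of 0.9 to 0.5. These figures rest on unadjusted one-sided testing, which the article neither states nor rules out, and on correlations that it does not give. The evidence shows that the stated 5% and 80% have not been tied to the hypothesis. It does not show that the trial will exceed 5%. The weight is moderate: it affects what may be concluded, and it can be corrected in the text.

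**What to change.** 1. Name IAT at one stated visit as the single primary outcome, and list DSM-5 and the digital addiction scale as secondary.
2. Choose one of two structures:
   - keep both claims against control and test them in a pre-stated order, each at the full level, or by Hochberg; or
   - replace H1 with the one randomised contrast, P against N. This also avoids resting the confirmatory claim on an external, non-randomised control. The direction should be stated in advance, because 72 per group is derived for a one-sided test.
3. Say what the 80% refers to. At 72 evaluable per group and a 0.20 difference, it holds for a single test or the first in an ordered sequence. If the 5% is split, state about 70% per arm, and about 84-91% for at least one arm if both work.

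**Cost.** H1, the primary objectives, the power statement and the analysis section must be reworded. No extra participants are needed. The price is a less favourable per-arm power statement and fewer co-primary claims. Only if 80% per arm is wanted with a split 5% would recruitment rise, from 80 to 103 per group.

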## Methods

### Study Design

A 3-arm superiority randomized controlled trial will be performed. The study flow is depicted in Figure 1. Patients with gadget addiction will be selected from the Kaumarbhritya Outpatient Department of MGACHRC Salod, Wardha as per inclusion criteria mentioned in Textbox 2. During the first visit, Parents will be asked whether they would like to deaddict their child from gadget addiction if they are willing then written informed assent will be obtained from the participants’ guardian. Participants will then complete questionnaires on the internet addiction test scale and digital addiction scale. Furthermore, participants’ social behavior and Prakruti (physical and mental constitution) will be assessed. As well as age, gender, socioeconomic status, and type of gadget he or she is using frequently, and the purpose of gadget use will be assessed. After this period, participants will be randomly allocated to both intervention groups in a 1:1 allocation ratio. After this, Medhya Rasayana will be prescribed to participants in group I according to age-wise doses at a frequency of twice a day for a period of 90 days as mentioned in Table 1. Participants allocated to group II will be counseled regarding the adverse effects of gadget addiction on physical and mental health and advised to follow the following routine daily for a period of 90 days, details of nonpharmacological interventions are described in Tables 1 and 2. Yoga (sun salutations, meditation), Targeted reduction in Gadget use time Padanshik krama, that is, reduce gadget use time by one-fourth part each week. Reduced time will be used for adventure, bravery, cognitive skill-oriented things, sports, and yoga. Patients will be counseled to play indoor and outdoor games daily. Encouragement toward attending social programs whenever required and feasible, encouragement of parent-child relationship by advising parents to spend a minimum of 2 hours of quality time daily with children and to give a reward for not using mobile with encouraging children to learn new things, participate in group activities with peers and teach etiquette. Initial training in sun salutation and the method of meditation will be given to participants and their parents at the time of enrollment. Children will be asked to do the proposed sun salutation and meditation on the assessment day. Participants not responding or not following instructions will be eliminated from the study. Group III will be the external group due to the fact that cognitive behavioral therapy requires trained professionals and there are time and financial constraints as well. Hence, in this published data of previously conducted clinical trials, cognitive behavioral therapy intervention in the management of gadgets or internet addiction will be used for comparison with Medhya Rasayana and Ayurveda nonpharmacological interventions. On the 30th, 60th, and 90th days of treatment, participants will be evaluated using the internet addiction test scale and the *DSM-5* (*Diagnostic and Statistical Manual of Mental Disorders, Fifth Edition*) scale for social behavior. A follow-up will be conducted on the 180th day to determine whether the intervention’s possible effects are lasting.

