While conducting the study, the investigator may face difficulties at the level of overdiagnosis of gadget addiction in children due to overconscious parents. Another difficulty we may face in the Ayurveda nonpharmacological intervention group is the failure to follow lifestyle modifications and yogic practices. This is the first study in the Ayurveda domain using pharmacological and nonpharmacological interventions for gadget addiction. Hence the small sample size and lack of a proven Ayurvedic control group are the main limitations of this study.

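### Eliminating randomised children for not responding or not following instructions inflates within-arm change and the external CBT comparison, and takes away the protection of randomisation for P versus N

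*Protocol article*

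**What the plan says.** The Study Design section randomises between the two internal groups: "participants will be randomly allocated to both intervention groups in a 1:1 allocation ratio". It then describes Medhya Rasayana (group P) and the nonpharmacological routine (group N). At the end of the group N description it adds a check: "Children will be asked to do the proposed sun salutation and meditation on the assessment day". The next sentence is the rule at issue: "Participants not responding or not following instructions will be eliminated from the study". It gives no definition of *not responding*, no time point and no arm, and it removes children from the study, not only from treatment.

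The comparator lies outside the trial: "Group III will be the external group due to the fact that cognitive behavioral therapy requires trained professionals". Published CBT results are used instead.

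Other relevant places in the protocol article:
- Primary objectives: the first two concern the efficacy of each Ayurveda arm; the third compares the three modalities. The alternative hypothesis is superiority over the control group.
- Participants: "To account for a 10% dropout rate, the sample size is increased to 80 per group".
- Dropout: covers only children who choose to stop.
- Statistical Analysis: names repeated measures ANOVA and chi-square, but no analysis set.
- Principal Findings: "Another difficulty we may face in the Ayurveda nonpharmacological intervention group is the failure to follow lifestyle modifications and yogic practices".

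**The concern.** The rule conditions membership of the study on what happens after allocation. If it means clinical non-response, it removes failures directly. If it means failing to carry out the routine, it removes non-adherers, who may well do worse. If it means not replying, it removes children whose outcome is unknown. In each case those left are a selected subset.

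Three comparisons are affected in different ways:
- Within-arm change is inflated when the removed children have the poorer outcomes.
- The comparison of each arm with published CBT data is inflated in the same direction, because the rule cannot act on the external data.
- P versus N is the only randomised comparison. It stops being a comparison of the groups as randomised, and any imbalance in removal between the arms becomes bias.

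The loss cannot be repaired at analysis, because the outcomes of eliminated children would not be collected.

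**Working it through.** **Inputs from the protocol article (Participants section).** P1 = 0.622, P2 = 0.362, difference 0.20, z values 1.64 and 0.84, 72 per group raised to 80.

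**The plan's own figure.** Read with the brackets that it needs:
(1.64 + 0.84)² × [0.622 × 0.378 + 0.362 × 0.638] / 0.20² = 6.1504 × 0.466072 / 0.04 = 71.66, so 72. Then 72 / 0.90 = 80. The figure reproduces, and the allowance is 8 children per arm.

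**Assumptions not in the documents.** The fraction removed, how strongly removal relates to outcome, and which arm loses children. Ranges are shown for each.

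**1. Proportion scale, within an arm.** If a share f of the children still addicted at the endpoint is eliminated, the apparent proportion is p(1 − f) / (1 − pf).

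| f | True 0.362 appears as | True 0.622 (no effect) appears as |
|---|---|---|
| 10% | 0.338 | 0.597 |
| 25% | 0.299 | 0.552 |
| 50% | 0.221 | 0.451 |

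Example: 0.362 × 0.75 / (1 − 0.362 × 0.25) = 0.2715 / 0.9095 = 0.299. With no effect at all, f = 25% or 50% produces a spurious fall of 7 or 17 percentage points.

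**2. Against the external data.** Take the comparator as known at 0.362, with the arm truly equal to it and 80 children before removal. By normal approximation, the one-sided 5% error becomes about 11%, 29% and 80% for f = 10%, 25% and 50%.

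**3. P versus N, proportion scale, both truly 0.362.**
- Removal of 25% or 50% of failures in N only: a spurious 6 or 14 points in favour of N, with two-sided rejection in about 13% or 48% of trials.
- The same removal in P only: the same size in favour of P.
- Equal removal: difference 0. Where there is a true difference (0.562 versus 0.362), equal removal of 25% or 50% shrinks it from 0.200 to 0.192 or 0.170.

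**4. P versus N, mean scale.** Set-up: normal outcome, 80 per arm, no true effect, removal in N only, Welch test, 20,000 simulated trials. Nominally 2.5% of trials favour N, which is one tail of a two-sided 5% test. (The plan's sample size uses a one-sided 5% instead.) The mean shift after removing the worst fraction f is φ(z_f) / (1 − f). If removal follows adherence with correlation r to outcome, multiply by r.

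| Removed | Shift, r = 0.3 | Shift, r = 0.5 | Shift, worst by outcome | False 'N better', r = 0.3 | r = 0.5 | worst by outcome |
|---|---|---|---|---|---|---|
| 10% | 0.06 SD | 0.10 SD | 0.19 SD | 6% | 9% | 26% |
| 20% | 0.10 SD | 0.17 SD | 0.35 SD | 9% | 19% | 63% |
| 30% | 0.15 SD | 0.25 SD | 0.50 SD | 13-14% | 31% | 89% |

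Hand check of the smallest entry: SE = √(1/80 + 1/72) = 0.162; 0.0585 / 0.162 = 0.36; P(Z > 1.96 − 0.36) is about 5.5%.

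If both arms lose the worst 10-30% equally, a false 'N better' occurs in about 4-7% of trials.

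**5. Dropout allowance.** Expected failures per arm at 0.362 are 80 × 0.362 = 29. The 8 spare children are used up once 8 / 28.96 = 28% of them are eliminated, if elimination comes on top of ordinary dropout.

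**The case against.** A reader might infer that the rule biases every comparison towards benefit. The documents do not support that. P and N are both active arms, so a bias that favours one works against the other, and similar losses in both largely cancel.

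A reader might also infer that treatment failures are certainly deleted. The rule follows directly on the yoga and meditation check, so *not responding* can mean failing that check. On this reading it removes non-adherers rather than failures as such, and it may apply to group N alone.

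The 26-89% error rates must not be the headline. They need removal in N only, which comes from the adherence reading, together with perfect selection on outcome, which comes from the clinical reading and gives no reason to spare P. They are a worst case.

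Nor is it certain that N loses more children. The Discussion says only that non-adherence may occur there, the rule is not expressly limited to N, and a twice-daily oral medicine can also go untaken. The protocol does not say whether elimination is already counted in the 10% dropout.

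All of this stands, and it limits direction and size. It does not remove the defect, because every reading selects after randomisation. A statistical analysis plan that is not shown could define an intention-to-treat set, but it could not supply outcomes that were never collected.

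**Conclusion.** The rule is wrong as written and should be changed. It inflates within-arm change, which is the subject of the first two primary objectives, and each arm's comparison with the external CBT data, provided that removed children do worse than those who stay. It also removes the protection of randomisation for P versus N. The direction there depends on which arm loses more children; the yoga check and the foreseen non-adherence make a bias towards N plausible, not certain.

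The adherence scenario in step 4 is the fairer guide to size for P versus N: a multiple of the nominal error, though far below the worst case. For the external comparison, even removal of 10% of failures roughly doubles the nominal 5% error when the comparator rate is taken as known.

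**What to change.** Delete the elimination sentence and state instead: *All randomised children, except those who withdraw consent, continue to be assessed at the planned visits and are analysed in the arm to which they were allocated, whatever their response or adherence. Non-adherence is recorded. A per-protocol analysis is secondary only.* The authors should also say what *not responding* means. The exception for withdrawal keeps the text in line with the Dropout and Informed Consent sections. Whether a child's treatment stops is a separate clinical matter and is not addressed here.

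The cost is small: a change of text and continued questionnaires on days 30, 60, 90 and 180, which are already scheduled. There are two downsides. The estimated effect may be smaller, and the outcomes of children who cannot be reached must be handled as missing data.

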**Methods:**

A randomized, parallel, triple-arm interventional study will be conducted on diagnosed participants of gadget addiction with an age group of 6- to 16-year-old children, which will be selected and equally distributed in 2 groups. Group P will be given Medhya Rasayana (pharmacological intervention), group N will be nonpharmacological Ayurveda intervention, and group C (cognitive behavioral therapy) will be an external group. The Study duration is 180 days with assessment at baseline, midpoint, and endpoint Appropriate statistical techniques, such as ANOVA and regression analysis, will be used to examine the data and evaluate the efficacy of the 3 groups’ interventions. We will perform subgroup analysis according to initial addiction severity, gender, and age. Primary outcome measures include a reduction in gadget addiction and changes in the psychosocial well-being of participants. Standardized questionnaires and instruments will be used to collect data.

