#### Adverse Effects

Adverse consequences are characterized as unfavorable results resulting from study involvement. This study’s potential side effects may include injury while doing yoga or Gastrointestinal system disturbances due to Medhya Rasayana avaleha. Adverse effects that occur will be noted and assessed for both the intervention and control groups.

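### The formal hypotheses test superiority over an external CBT group that is not randomised, while the only randomised contrast (P versus N) has no formal hypothesis and no sample-size basis

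*Protocol article*

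**What the plan says.** The Study Design section opens with "A 3-arm superiority randomized controlled trial will be performed". It then says that "participants will be randomly allocated to both intervention groups in a 1:1 allocation ratio", and that "Group III will be the external group due to the fact that cognitive behavioral therapy requires trained professionals". Published results of earlier CBT trials are to be used for the comparison. Table 1 gives 80 participants for group P, 80 for group N and no number for group C, whose duration and assessments are marked not applicable. The abstract also speaks of a triple-arm study, yet has participants "selected and equally distributed in 2 groups".

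The null hypothesis is that the two Ayurveda interventions "are not as effective as the control group in reducing gadget addiction in children". The alternative is "At least 1 intervention among the Medhya Rasayana and Ayurveda nonpharmacological intervention are more effective than the control group". The paragraph under H1 gives the purpose as finding out whether the three interventions differ, and says that the null hypothesis will be tested on data gathered in the randomised trial.

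P versus N falls within the general aim under Study Objectives and within the third primary objective, which compares all three modalities. The Conclusion section is about the relative effectiveness of P and N. The abstract assigns ANOVA and regression to evaluating the three groups. The Adverse Effects section states: "Adverse effects that occur will be noted and assessed for both the intervention and control groups".

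**The concern.** The label, the hypotheses and the source of the data do not fit together. A reader of the eventual report would take a finding that Medhya Rasayana or the nonpharmacological programme is better than the control as the result of a randomised trial. In fact it would compare children recruited around one hospital with published samples that may differ in age, severity, country, measurement and calendar time. Randomisation between P and N does nothing to balance those differences.

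The contrast that randomisation does protect, P versus N, is the one the article concludes about. It has no formal hypothesis, and the sample size was not derived for it. The trial could therefore end with a headline claim it cannot support and a randomised comparison whose precision nobody has stated.

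**Working it through.** **1. Which groups are randomised, and what the hypotheses compare**

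| Element | Where | P | N | C (CBT) |
|---|---|---|---|---|
| Randomised 1:1 | Study Design | yes | yes | no |
| Participants | Table 1 | 80 | 80 | external, none enrolled |
| Data gathered in this trial | Table 1 | yes | yes | no |
| Role in H0/H1 | Hypothesis | tested intervention | tested intervention | comparator, by inference |

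The article does not define the control group. P and N are named as the interventions and no other arm is recruited, so only the CBT group can be meant. H0/H1 therefore need CBT data, and the trial that is said to supply the data gathers none.

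**2. The plan's own sample size**

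Inputs from the Participants section: z values 1.64 and 0.84, P1 = 0.622 (initially), P2 = 0.362 (after the intervention), δ = 0.20, dropout 10%.

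- Variance term: 0.622 × 0.378 + 0.362 × 0.638 = 0.2351 + 0.2310 = 0.4661.
- n = (1.64 + 0.84)² × 0.4661 / 0.20² = 6.1504 × 0.4661 / 0.04 = 71.66, rounded up to 72.
- With dropout: 72 / 0.9 = 80.

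Both figures reproduce, so the arithmetic is not at fault. The value 1.64 makes the test one-sided at 5%; a two-sided 5% test with the same inputs would need 91.5. The two proportions are a before/after pair. They are neither a P versus N difference nor an Ayurveda versus CBT difference.

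**3. What 72 evaluable per arm gives for P versus N**

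The article gives no P versus N difference. *Assumption:* one arm ends at 0.362; two-sided 5%.

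For a 20-point difference (0.362 versus 0.562; mean 0.462):

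- Unpooled SE = √[(0.2310 + 0.2462)/72] = 0.0814.
- Pooled SE = √[2 × 0.462 × 0.538/72] = 0.0831.
- Power, pooled SE under H0: Φ[(0.20 − 1.96 × 0.0831)/0.0814] = Φ(0.456) = 68%.
- Power, unpooled SE throughout: Φ(0.20/0.0814 − 1.96) = Φ(0.497) = 69%.

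By the pooled method:

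| True P versus N difference | 5 points | 10 | 15 | 20 | 25 |
|---|---|---|---|---|---|
| Power, 72 per arm | 9% | 23% | 44% | 68% | 86% |

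The smallest difference detectable with 80% power is about 23 points. A 20-point difference at 80% power would need 97 evaluable, or 108 recruited, per arm.

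**4. Exposure of a comparison with published CBT data (illustration only)**

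The article gives no CBT sample size or result. *Assumptions:* 72 analysed here, 50 to 100 in the published sample, no true treatment difference, a 0.2 SD difference between populations or measurements, two-sided 5%.

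- SE = √(1/72 + 1/n_ext): 0.184 for 50 and 0.155 for 100.
- Shift in SE units: 0.2/0.184 = 1.09 and 0.2/0.155 = 1.29.
- P(|Z + shift| > 1.96) = 19% and 25%, against a nominal 5%.

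On the scale and sidedness of the Participants section (proportions, one-sided 5%), assume 72 in each group and a true rate of 0.362 under both treatments. If the published CBT rate is worse by 5, 10 or 15 points for reasons other than treatment, superiority is falsely declared in about 15%, 33% or 57% of trials.

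**The case against.** The external status of the CBT group is disclosed in the abstract, in Study Design (with a reason) and in Table 1, and external controls can be legitimate. That stands: nothing is concealed. Disclosure does not, however, turn a non-randomised comparison into the target of a randomised superiority test. The limitations in the Discussion mention the small sample and the lack of a proven Ayurvedic control, not the non-randomised CBT comparison. An SAP could specify how the external data are handled. It could not randomise group C, and moving the hypothesis to P versus N would contradict H0/H1 as printed.

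Some stronger readings are tempting but not supported:

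- *That P versus N is absent from the plan.* It is in the objectives and in the stated purpose of the hypothesis. Only the formal H0/H1 and the sample-size calculation omit it.
- *That H0 and H1 leave out equality, so rejecting H0 would show only non-inferiority.* A 5% test of worse than control has its size fixed at the boundary, which is equality. Its rejection region is therefore that of a test of worse or equal. The wording is loose but changes no inference.
- *That published CBT results will enter the ANOVA as if they were a concurrent arm, or be treated as a fixed benchmark.* The abstract's sentence on three groups invites the first reading, but the Statistical Analysis section does not put group C in any test and leaves the choice of method to a statistician. Nothing mentions a fixed benchmark.
- *That the error rates above are properties of this trial.* They depend on assumed sample sizes and shifts. A shift that disfavours the Ayurveda arms would lower the risk of a false superiority claim.

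The adverse-effects sentence is a minor slip and adds nothing to the weight of the point.

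**Conclusion.** The point holds as a contradiction within the article. The study is labelled a three-arm randomised superiority trial but has two randomised arms, and its formal hypotheses are directed only at a comparator for which the trial gathers no data. Followed as written, the plan would present a non-randomised comparison as a randomised result. This needs correcting before analysis.

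The one inference in that conclusion is that the control group means CBT; no other comparator exists. The 19–25% false-significance figure shows how sensitive such a claim is to a modest population difference and is not an estimate for this trial. The power of about 68–69% for a 20-point P versus N difference, and the detectable difference of about 23 points, rest on one arm at 0.362, 72 evaluable per arm and a two-sided 5% test.

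**What to change.** - Describe the study, in the abstract and in Study Design, as a two-arm 1:1 randomised trial of P versus N with an external CBT reference.
- Replace H0/H1 with hypotheses for P versus N on the primary addiction outcome: no difference against a difference, two-sided.
- Reword the third primary objective and the abstract's sentence on ANOVA and regression so that the randomised analysis covers P and N only.
- Present published CBT results as a non-randomised, descriptive comparison with intervals and no confirmatory superiority claim.
- Correct the Adverse Effects sentence, since no control children are enrolled.
- State that 80 per group was not sized for P versus N, give the power or precision it provides for that contrast with the assumptions, and say that a non-significant P versus N result is not evidence of equivalence.

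The cost is wording in the protocol and the registry entry, with no new participants or procedures. The trial gives up a confirmatory claim against CBT and has to state a less favourable power for its randomised comparison.
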